### Sample size

We conducted an a priori power analysis using G*Power 3.1 [80] to calculate the appropriate sample size. Using an α value of 0.05, power of 0.80, and a medium effect size (*f* = 0.38) for video-game training [45] and physical training [81], and four groups within the *F*-test family, a total sample size of 124 is required. Considering a dropout rate of 12%, a total of 144 participants would be sufficient to detect significant main effects. According to this calculation, the adequate number of participants in each group (multidomain training, video-game training, physical activity training, and active control) is 36. According to this, we will set a sample size of 36 participants per arm, which is adequate for the experimental design. According to Montgomery et al. [82], with this number of participants the design would be underpowered to detect an interaction effect, as it would need a fourfold increase in sample size. However, given that lower interaction effects would not be clinically relevant, we decided to maintain our initial sample size estimation.

In the elaboration of this protocol, we have followed the SPIRIT 2013 explanation and elaboration guidance for reporting protocols of clinical trials [83].

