### General procedure

After baseline, participants who meet the inclusion criteria will be randomly assigned to one of the four groups. The active control group was introduced in the design to control for placebo effects [84]. The main question is whether the multidomain group will outperform the single-domain groups at posttest, and whether these groups will outperform the active control group in a series of cognitive-control and memory tasks (see below). We focused on these cognitive domains because they deteriorate with age and are critical for independent living.

All methodological designs of primary and secondary outcomes are constructed using the rules of counterbalance and stimulus rotation. Response keys will be counterbalanced across conditions. The computerized tasks have been programmed with E-Prime 2.0 (Psychological Software Tools Inc.). Continuous EEG activity will be recorded in our laboratories with thin electrodes from 40 scalp sites using NuAmps amplifiers while participants perform the task-switching task.

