### Statistical analysis

All data from participants with complete baseline assessment and who attended at least one training session will enter into a primary intention-to-treat analysis. For the secondary per-protocol analysis, only the data of participants with a complete cognitive assessment and an attendance rate ≥ 70% will be considered.

Executive functions (set shifting, maintenance, inhibitory control) and memory functions (short-term, visual, and verbal immediate and delayed memory) will be assessed at pretest, posttest, and follow-up. The statistical analysis corresponding to the behavioral results will be carried out with the SPSS statistical package for Windows (SPSS 25.0; IBM Corporation). Results will be considered significant at *p* < 0.05, with Bonferroni-corrected post hoc tests performed as appropriate. We will explore the missing data to ascertain their pattern and will apply an adequate technique of multiple imputation. Repeated ANOVA measures will be conducted with four groups (multidomain training, cognitive training, exercise training, active control) at three time points (pretest, posttest, follow-up) to test the primary hypothesis (i.e., differences in efficacy between interventions compared to the active control condition). Repeated ANOVA measures will also be performed to determine the effect of the interventions on secondary outcomes. To evaluate the effect size of the combined multimodal group versus each individual intervention group and the control arm, we will use multimodal regression with an interaction term. Electrophysiological data will be analyzed with CURRY 8.0.2, the EEGLAB toolbox [92], and the ERPLAB plugin for EEGLAB [98].

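### The main question's pre-set comparisons are tested only by Bonferroni post hoc tests, which costs power that a claim of beating both single-domain arms need not give up

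*Protocol article*

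**What the plan says.** Under General procedure, the main question is "whether the multidomain group will outperform the single-domain groups at posttest, and whether these groups will outperform the active control group". Objectives and hypotheses gives the same direction and expects the multidomain condition to do better than each of the two single-domain conditions.

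Statistical analysis specifies a four-group by three-time repeated-measures ANOVA for the primary hypothesis, which it words as differences from the active control condition. It sets the significance level at 0.05, "with Bonferroni-corrected post hoc tests performed as appropriate". The number of comparisons in the Bonferroni family is not given. The same section plans a regression with an interaction term for multidomain against each other arm. Its stated purpose is to evaluate effect size, and no decision rule is attached to it.

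Sample size uses an omnibus effect: "four groups within the *F*-test family, a total sample size of 124 is required". It then states: "Considering a dropout rate of 12%, a total of 144 participants would be sufficient to detect significant main effects". No pairwise difference between arms is given.

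**The concern.** The comparisons that answer the main question are few, directional and known before the data. The plan treats them as follow-up tests to an omnibus F-test, under a correction suited to searching all pairs of arms.

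Two kinds of claim are mixed here. Beating both single-domain arms requires two successes, so it is an intersection-union claim: the requirement to win twice already guards against a false claim. Beating control with any one of several arms can succeed by more than one route, so it does need a correction, but Dunnett and Holm hold the same familywise error as Bonferroni and reject more often. With 36 participants per arm, the power given up is not trivial.

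**Working it through.** **The plan's own figure.** For a one-way F-test with four groups, alpha 0.05 and f = 0.38, the noncentrality is N × 0.38². Power reaches 80% at N = 80, not 124; at N = 124 it is 95%. The planning effect is therefore unclear, which is a separate matter, but it is one reason to show a range below. The dropout step is acceptable: 124 / 0.88 = 140.9, rounded up to 36 per arm = 144.

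**Inputs.** Completers per arm: 36 × 0.88 = 31.7, taken as 32. Pooled-variance t-tests have 4 × 32 − 4 = 124 degrees of freedom. Two-sided tests and a six-pair family (all pairs of four arms) are assumptions; the protocol states neither.

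**False-claim rate without correction.** The worst case is multidomain equal to one single-domain arm and far above the other. A false claim then needs one test to reach p ≤ 0.05 in the favourable direction: 0.05 / 2 = 2.5%. With all arms equal, simulation gives 0.5%.

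**From f = 0.38 to differences between arms (in SD).**
- Additive means 0, a, a, 2a: SD of the means is a/√2, so a = 0.38 × √2 = 0.537.
- f = 0.38 for each two-level main effect: difference 2 × 0.38 = 0.76.
- Only multidomain differs, means 0, 0, 0, a: SD is a√3/4, so a = 0.38 × 4/√3 = 0.878.
- Evenly spaced means over a range r: SD is r√5/6, so r = 1.02; multidomain exceeds the two single-domain arms by 0.34 and 0.68.
- 0.38 read as the pairwise difference itself, with additive means.

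**One comparison, additive case.** Noncentrality = d√(n/2) = 0.537 × √16 = 2.15. Critical t is 1.979 at 0.05 and 2.681 at 0.05/6. Power is 57% and 30%.

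**Both comparisons.** The two tests share the multidomain arm (correlation 0.5), so joint power was simulated with 400,000 draws:

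| Reading of 0.38 | Each at 0.05 | Bonferroni, six pairs |
|---|---|---|
| Additive, overall f = 0.38 | 41% | 16% |
| Each main effect f = 0.38 | 76–77% | 49% |
| Only multidomain differs | 89% | 68% |
| Evenly spaced means | 25% | 8% |
| Pairwise d = 0.38 | 18% | 5% |

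In the additive case, a smaller Bonferroni family gives 29% (two tests) or 24% (three), and Holm over six pairs gives 22%. At 36 per arm with no dropout, the additive pair is 46% and 20%.

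**Single-domain arm against control, additive case.** Bonferroni over six pairs 30%, Bonferroni over three 39%, Dunnett for three arms against control (critical value 2.377) 41%. Most of this gain comes from limiting the family to the three relevant comparisons.

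**The case against.** The strongest objection is that no section sets a both-must-win rule. The expectation about both single-domain arms is a hypothesis, and the ANOVA sentence words the primary hypothesis against control. A claim on one single-domain arm alone, or on any one arm against control, does need a correction. This stands: the argument for testing each at 0.05 is conditional on a rule that the text implies but does not state.

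It may also be said that family size is a detail for an analysis plan, that Bonferroni is valid, and that the interaction regression covers the same comparisons. The family size is indeed open. But the article does choose a method, that method suits the stated question poorly, and the regression is described for effect size without a test that settles the question.

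A further objection is that the correction gives incidental protection across outcomes. The protocol lists six primary behavioural tasks plus ERP measures and states no correction across them. In the worst case with six independent outcomes, a 2.5% rate each gives 1 − 0.975⁶ = 14% for at least one false claim, against about 2.5% if each test uses 0.05/6. This also stands. The answer is an explicit rule across outcomes, not an unspecified pairwise correction that happens to help.

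A reader might infer that the main question needs no correction at all, or that power falls from 41% to 16% at the plan's own effect size, or to 8% with 18 tests over three visits. The documents support none of these. f = 0.38 is an omnibus effect with no arm pattern. The additive pattern assumes no interaction, although the stated aim is synergy. The family of six is not stated, and a family of 18 has no basis because the main question is placed at posttest.

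**Conclusion.** The point holds in conditional form. The pre-set comparisons have no planned contrasts, and the only significance tests named for them carry an unspecified Bonferroni correction. If the claim is that multidomain beats both single-domain arms, that correction is not needed within an outcome. Against a six-pair family it costs 13 to 28 percentage points of power across the five readings tried. The direction of the loss is secure. Its size is not, because it rests on the arm pattern, 32 completers per arm, simple two-sided t-tests and the family size.

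Dropping the correction does not make the trial well powered: in the additive case, power to beat both is still only 41%.

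**What to change.** In Statistical analysis, replace the post hoc sentence with the following:

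1. Multidomain against CI + EC and against EI + CC at posttest are planned contrasts. Multidomain is declared to outperform both only if each has two-sided p ≤ 0.05 in its favour.
2. The three trained arms against active control are tested with Dunnett or Holm.
3. A claim on one single-domain comparison alone, and all remaining pairs, use Holm.
4. These rules control error within one outcome. Multiplicity across the primary outcomes is handled by a separate, stated rule.

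The text should also say that items 1 to 3 carry separate error budgets, if that is intended, and give power for item 1 under a stated pairwise difference.

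The cost is a few sentences and no extra participants. The price is that the false-claim rate for beating both rises, to at most 2.5% per outcome, and a claim on one comparison still needs correction.

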### Data monitoring committee and data management

Personal information about participants obtained during the individual interviews as well as performance data and all study-related information will be coded in a database and stored securely at the study site to maintain participant confidentiality. A coded identification (ID) number to maintain participant confidentiality will identify all data collection and administrative forms. The electronic data will be stored securely on a university computer and a high-drive disc (HDD) that are password protected. Paper copies as well as HDDs will be securely stored in a locked cabinet at the study site. All forms, lists, appointment records, consent forms, and any other listings that link participant ID numbers to other identification information will be stored in a separate, locked file in a limited access area. Only the members of the researcher team directly involved in data collection, maintenance, and management will have access to the data set.

The data monitoring committee (DMC) will be composed of [name] and [name], who will regularly check on the correctness of data collection and encoding and its correspondence with the entrances in the laboratory diary. The DMC will be responsible for securing the data on a weekly basis on the aforementioned devices. The data will be stored securely in our laboratory for 5 years.

We have not planned to conduct subgroups of interim analyses.

### Steering committee

The steering committee will meet at least on a quarterly basis to monitor the trial processes, independently of the funding organization. The committee will check compliance with the assessment and training protocols and the timelines, and will oversee and manage the trial. Its members, who form an active part of the research group, are SB and [name]. They will verify trial processes, such as participant enrollment, informed consent, eligibility, allocation of participants to groups, and adherence to trial interventions.

### Dissemination plans

After completion of the trial, the results will be presented at international and national conferences and will be published in appropriate scientific journals. We will also deliver the results to the participants.

## Discussion

We investigate the potential for cognitive training and physical exercise to prevent or minimize the negative effects occurring with aging. This clinical trial examines the efficacy of a combined intervention on moderate cognitive decline as well as affective well-being and physical condition in healthy older adults. This multimodal intervention study will contribute to the increasing body of literature investigating ways to promote brain plasticity and maintain healthy and active aging.

To summarize, cognitive decline and physical decline have negative effects in older adults and impact negatively on society due to the increasing number of older adults that will suffer cognitive decline and neurodegenerative diseases in the next decades. Finding effective ways to prevent the negative impact of declining cognition would have a key effect on the current limited social and health care resources.

## Trial status

This clinical trial was registered at the National Institute of Health (NIH) with the Clinicaltrials.gov identifier NCT03823183 (https://register.clinicaltrials.gov/ClinicalTrials.gov) on 21 January 2019. The protocol version number is number 1 (January 2019). Recruitment started in February 2019 and is expected to be completed in February 2020. Once the trial is completed, results will be reported according to the Consolidated Standards of Reporting Trials (CONSORT) guidelines. The trial is active and ongoing. We expect to have the final results by the middle of 2021.

## Data Availability

Access to the protocol and the dataset may be provided upon request to the authors.
